## Abstract

**Background:**

Many patients with a non-affective psychotic disorder suffer from impairments in social functioning and social cognition. To target these impairments, mentalization-based treatment for psychotic disorder, a psychodynamic treatment rooted in attachment theory, has been developed. It is expected to improve social cognition, and thereby to improve social functioning. The treatment is further expected to increase quality of life and the awareness of having a mental disorder, and to reduce substance abuse, social stress reactivity, positive symptoms, negative, anxious and depressive symptoms.

**Methods/design:**

The study is a rater-blinded randomized controlled trial. Patients are offered 18 months of therapy and are randomly allocated to mentalization-based treatment for psychotic disorders or treatment as usual. Patients are recruited from outpatient departments of the Rivierduinen mental health institute, the Netherlands, and are aged 18 to 55 years and have been diagnosed with a non-affective psychotic disorder. Social functioning, the primary outcome variable, is measured with the social functioning scale. The administration of all tests and questionnaires takes approximately 22 hours. Mentalization-based treatment for psychotic disorders adds a total of 60 hours of group therapy and 15 hours of individual therapy to treatment as usual. No known health risks are involved in the study, though it is known that group dynamics can have adverse effects on a psychiatric disorder.

**Discussion:**

If Mentalization-based treatment for psychotic disorders proves to be effective, it could be a useful addition to treatment.

**Trial registration:**

Dutch Trial Register. NTR4747. Trial registration date 08-19-2014.

## Background and rationale

Non-affective psychotic disorders (NAPD) like schizophrenia are accountable for a substantial part of the total burden of disease, constituting the fifth and sixth leading cause of disability in the world, for men and women respectively [1]. A major contributor to this high level of disability is thought to be the decline in social functioning associated with NAPD. Patients with NAPD experience difficulty communicating [2], and tend to have poor social problem-solving skills [3]. These social deficits are predictive of poor vocational outcome [4] and poor quality of life [5]. It is surprising, therefore, that few treatments have been developed to effectively target them.

Social cognition – defined as “the ability to construct representations of the relation between oneself and others, and to use those representations flexibly to guide social behavior” [6] has been identified as one of the strongest predictors of social functioning in patients with NAPD [7]. Examples of social cognitive impairments in NAPD include difficulties recognizing emotions [8], empathizing [9] taking another person’s perspective [10] and understanding social hints [11]. In recent years just a few treatments, mostly rooted in cognitive/behavioral theory [12–14], have been developed that target social cognition. Results, are preliminary, but do suggest that impaired social cognitive deficits are targetable by psychosocial interventions [13–15].

Mentalization-based treatment for psychotic disorder (MBT-P) is based on a manualized psychodynamic treatment for Borderline Personality Disorder (BPD) [16]. Recent prospective studies suggest that psychodynamic therapy may improve global functioning in NAPD [17, 18], although randomized controlled trials should be conducted to substantiate this claim. Also, metacognitive psychotherapy [19] – which is closely related to MBT [20] – holds promise as a treatment for patients with schizophrenia [21]. MBT-P was developed to specifically improve social functioning by targeting the social cognitive process called ‘mentalizing’. Fonagy and colleagues [22] describe mentalizing as “the process by which we implicitly and explicitly interpret the actions of ourselves and others as meaningful on the basis of intentional mental states”. MBT adheres to a few important principles: (i) The therapist focuses on the current mental state of the patient to practice making representations of internal states; (ii) the therapist focuses on the present as opposed to the past; (iii) the therapist avoids talking about mental states that are not linked to subjectively felt reality; (iv) the therapist avoids talking about complex mental states; (v) the therapist focuses on recovering mentalizing, not creating insight [23].

This approach was found to reduce symptoms and interpersonal distress, and improve social functioning in patients with BPD [24]. Although BPD and NAPD may seem qualitatively different disorders, early views assumed borderline psychopathology occupied an area between neurosis and psychosis (e.g. Kernberg [25]) and could involve transient psychotic episodes. Since then, evidence has substantiated psychosis proneness in BPD. Psychotic symptoms, including hallucinatory experiences and delusions, occur regularly in patients with BPD, often persist over time, and are for a large part already present in early childhood [26]. In a recent study that included patients with either BPD or Schizophrenia, 17 % of participants met the criteria for both disorders [27]. Additionally, some NAPD and BPD patients share a tendency to excessively attribute incorrect intentions to others, or to “hypermentalize” [28–30]. Furthermore, disturbances in self-awareness and self-representation have been suggested to play an important role in both disorders [31]. Lastly, childhood trauma has been established as an important factor in the origins of both disorders [32]. Thus, as has been suggested earlier [20, 33], MBT may be a similarly suitable treatment for NAPD.

## Research aims and hypotheses

### Primary research aim

The primary aim of this study is to establish whether mentalization-based treatment for psychotic disorder (MBT-P) improves self-reported social functioning in patients with NAPD. We hypothesize that patients who receive MBT-P will show greater improvements in social functioning compared to patients who have had treatment as usual (TAU) only. We also expect that any difference observed will still be present at a 6 month follow-up.

### Secondary research aims

In addition to the self-reported level of social functioning, we will also examine global functioning as rated by researchers. Other outcome measures were chosen with previous research regarding MBT in mind. According to Fonagy and Bateman [34], MBT’s mechanism of change is improving patients’ mentalizing capacities. We therefore aim to establish whether MBT-P indeed increases mentalizing capacity, measuring several dimensions of social cognition, and whether this increase mediates a potential treatment effect. Furthermore, in earlier studies, Bateman and Fonagy [24] reported a reduction of anxious and depressive symptoms and of substance abuse. We expect similar results regarding NAPD patients. Given the strong relation between social functioning and quality of life, we assume that patients receiving MBT-P will report a higher quality of life. Additionally, based on previous research [35], we predict that improvement of social cognitive capacity will also lead to an increased awareness of having a mental disorder. Furthermore, as Bateman and Fonagy describe [34] that MBT was designed to improve emotion regulation in situations of attachment related (i.e., social) stress. Based on this, we assert that patients will have less aversive emotional reactions to situations of social stress as a result of MBT-P. If MBT-P can reduce patients’ emotional reactivity to social stress, they may also become less prone to develop positive psychotic symptoms, as social stress reactivity may be an affective pathway to psychosis [36]. Lastly, because social functioning and mentalizing ability have been found to be strongly related to negative symptoms, we will examine whether MBT-P reduces negative symptoms [37–39].

### Covariates

Certain potential effect modifiers will be taken into account. First, adverse childhood experiences such as neglect or physical, psychological, and sexual abuse have been associated with social dysfunction later in life [40]. Second, personality organization (PO) has been shown to impact psychotherapy treatment response [41] and the level of social cognition [42]. Five levels of personality organization (PO) are identified, each characterized by different levels of anxiety tolerance and different capacities for impulse inhibition or ‘control’: Neurotic PO (good anxiety tolerance, over-control); Borderline PO (moderate to poor anxiety tolerance, differing levels of control); Narcissistic Borderline PO (good anxiety tolerance, undercontrol); Latent Psychotic PO (moderate anxiety tolerance, weak control); and Manifest Psychotic PO (poor anxiety tolerance, weak control). Third, the awareness of bodily sensations has been regarded as the first level of emotional awareness [43], which is an essential part of social cognition [44]. Psychopathology usually is accompanied by (vague) physical complaints, called “somatization”. A failure to report physical complaints while suffering (severe) psychopathology may be indicative of an absence of bodily awareness and therefore an impaired social cognitive capacity. Fourth, medication use can affect social functioning in patients with NAPD, therefore the type of medication is registered and adherence to medication is measured. Fifth, MBT attendance is taken into account, because it is expected that those who attend more sessions will profit more. Sixth, baseline measurements of the outcome variables will be accounted for. Seventh, the duration of illness, because of its negative impact on functioning; and eighth, adherence to the MBT model by therapists, because it is likely to influence treatment outcome.

## Methods/design

### Trial design/setting

This study is a rater-blinded, randomized controlled trial. Patients referred to outpatient sites of the Rivierduinen mental health institute are randomly assigned to Treatment as Usual (TAU) plus MBT-P or TAU only. The Rivierduinen mental health institute provides in- and outpatient treatment to thousands of patients with psychiatric disorders in the Dutch province of South-Holland (e.g., Leiden, Gouda). The investigator and patients are aware of treatment allocation, but all measurements are performed by researchers blind to treatment allocation. Social functioning at baseline (t0) and after treatment (t2) will be compared for both treatment conditions. The patients are blind to this primary aim.

### Participants

Participants in the study are patients with NAPD (DSM-IV criteria [34]): schizophrenia, schizophreniform, or schizoaffective disorder (295.x), delusional disorder (297.1), brief psychotic disorder (298.8), or psychotic disorder not otherwise specified (298.9). At least 80 participants will be included from the Rivierduinen mental health institute.

Inclusion criteria are:At least 6 months of prior treatment.No more than 10 years of treatment for NAPD.Between 18 and 55 years of age.

Exclusion criteria are:Intellectual disability and/or illiteracy.A lack of mastery of the Dutch language.Substance abuse to such an extent that it necessitates inpatient detoxification. After detoxification the patient is still eligible for participation in the study. Patients cannot participate in a session while under the influence of drugs.

### Sample size calculation

The estimated effect size of the current study is based on two previous studies. A study examining the effect of MBT on BPD [35] showed moderate to large reductions of problems relating to interpersonal distress (d = 0.95; 95 %; CI: 0.59–1.30) and social functioning (d = 0.72; 95 % CI 0.37–1.06). A study concerning Social Cognition and Interaction Training (SCIT) – a treatment for patients with schizophrenia that shares many elements with MBT – showed large effects on social engagement (d = 1.77) and interpersonal communication (d = 1.57) on the Social Functioning Scale [36]. Based on these results, we expect to find a moderate to large effect of MBT-P on social cognition (i.e., a Cohen’s d of at least 0.7).

To calculate the required sample size, G*Power [37] was used. To obtain a significant difference with power equal to .80 with an independent samples t-test (for a true effect size of .7 and alpha = .05), 68 participants are needed. However, because repeated measurements (baseline and post-treatment) increase the power – depending on the test-retest reliability of the outcome measure – a smaller sample size is required. A formula has been devised [38] to account for the increased power when using multiple measurements: n_repeated measures_ = (1-ρ^2^)*n_t-test_; where ρ is the test-retest reliability of the scale used. Previous research has shown that the test-retest reliability of the social functioning scale after two and a half years is ρ = .40 [39]. Thus we need: (1-0.4^2^)*68 ≈ 58 participants to have 80 % power to find a significant difference.

It is difficult to predict the amount of drop-out in the study. In an unpublished pilot study, conducted at the Rivierduinen mental health institute, the drop-out rate of MBT-P within a period of 1 year was 10 %. Since the current RCT combines treatment and measurements, we estimate that the drop-out rate will be higher. Therefore, to be sure, we will recruit at least 40 (TAU) + 40 (TAU plus MBT-P) = 80 individuals. Even if 25 % of those initial patients (i.e., 20) drop out, there will be 60 patients left to detect an effect. Because patients in the MBT-P condition receive therapy in groups of up to eight persons, five groups will be formed in order to recruit 40 patients in the MBT-P condition.

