### Statistical analysis

#### Main effect

The main purpose of the statistical analysis is to compare the overall effect of treatment condition on social functioning. For this, an ANCOVA will be used with treatment condition as between-subjects variable, post-treatment social functioning as dependent variable, and baseline social functioning as a covariate. Other potential covariates include childhood trauma, level of PO, somatization of psychopathology, medication use, attendance of MBT-P sessions, duration of illness and adherence to the MBT-model by therapists. Similar analyses will be conducted for the secondary outcome measures (social cognition, quality of life, awareness of having a mental disorder, anxious, depressive, negative and positive symptoms and substance abuse).

Since drop-out will undoubtedly result in missing data, the possibility of attrition-bias is a cause of concern [72]. For example, it is conceivable that those who fare the worst in therapy tend to drop out, thus creating a biased sample. Following the advice of Altman [73], the analyses will therefore be conducted on the basis of ‘intention to treat’ (ITT), meaning that they will include all patients who sign up, regardless of actual participation in the entire program. Missing data will be handled by means of multiple imputation (MI) [74]. In the current case missingness is most likely to be caused by participants dropping out of their respective treatment programs. Since certain variables have been found to influence drop-out rates in patients with NAPD, we cannot assume that the data are missing at random. A review [75] identified a lack of insight, poor social functioning, positive symptoms, young age, male gender, a history of drug abuse, and unemployment as key predictors of treatment program drop out. Thus in the current study, these variables will be used to predict missingness. Additionally, treatment condition will be used as a predictor as well, because the time investment differs between conditions. For each analysis, a total of 5 imputed datasets will be created using a fully conditional Markov chain Monte Carlo (MCMC) approach, which will be combined using standard procedures [76].

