#### Multilevel analysis

Social stress reactivity is measured by ESM. This method generates data with a multilevel structure because there are multiple measurements per day for 5 days at a time for each patient. Since observations within patients tend to be more similar than observations from different patients, they are not independent. This necessitates a different (i.e., multilevel) analysis than the one used for the other outcome measures. Similar to Myin-Germeys and colleagues [78], differences in social stress reactivity between groups will be analyzed using mixed-effects regression models with treatment condition, the amount of stress during social situations, and their interaction term as independent variables, and positive and negative affect as dependent variables. The model will include random intercepts and random slopes for the stress predictor at the patient level, which allows for differences in overall levels of positive and negative affect across patients and for differences in the strength of the relationship between stress and these outcomes.

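### The sample size and the primary ANCOVA treat MBT-P patients as independent although they are treated in five therapy groups; with any positive within-group correlation the standard error is too small and the stated 80% power optimistic

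*Protocol article*

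**What the plan says.** Patients are randomised individually (Trial design/setting). Only the MBT-P arm has group therapy: one hour a week over 18 months (Duration and dose), at most eight patients, with one MBT-P therapist and one co-therapist at each session (Group therapy).

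In the Sample size calculation the groups appear only as a practical matter of reaching 40 patients: "Because patients in the MBT-P condition receive therapy in groups of up to eight persons, five groups will be formed". The calculation itself reads "To obtain a significant difference with power equal to .80 with an independent samples t-test" ("for a true effect size of .7 and alpha = .05"). This gives 68, which is then multiplied by 1 − ρ² with ρ = 0.40 to give about 58. The plan recruits 80 and relies on 60 remaining if 25% drop out.

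For the primary outcome, under Main effect, "an ANCOVA will be used with treatment condition as between-subjects variable", with baseline social functioning as covariate. No group or therapist term is listed. Therapist adherence is a potential covariate, but it does not represent membership of a group. Similar analyses are planned for the secondary outcomes.

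Under Multilevel analysis the article does recognise dependence, but only between ESM beeps of one patient: "Since observations within patients tend to be more similar than observations from different patients, they are not independent". It presents multilevel modelling as different from the analysis of the other outcomes.

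**The concern.** This is a partially nested design. One arm is clustered in five groups that share therapists and each other's company for 18 months; the other is not. The article gives reasons to expect some correlation within groups: it hopes that a group will foster belonging and attachment, and its abstract warns that group dynamics can do harm. Both are experiences that members of one group share.

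If the correlation is positive, the mean of the MBT-P arm is less precise than a single-level ANCOVA assumes. The p-value for the primary claim would then be too small and the power lower than planned. The article names the primary model and confines multilevel modelling to the ESM data, so this is an analysis that it fixes, not a detail left to a later plan.

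**Working it through.** **Inputs from the Sample size calculation:** d = 0.7, alpha = 0.05, power 0.80, ρ = 0.40, 40 + 40 recruited, 60 left after 25% drop-out, five MBT-P groups of up to eight.

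**Assumptions made here:** ICC 0.02 to 0.15 after baseline adjustment; equal total residual variance in the arms; drop-out spread evenly, so 30 per arm and five groups of 6 at N = 60; 40 per arm and five groups of 8 at N = 80.

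**1. The plan's own figure.** A two-sided t-test with d = 0.7 has power 0.7997 at 33 per arm and 0.812 at 34, so N = 68. (A one-sided test would need only 26 per arm, so the plan is two-sided.) Then (1 − 0.16) × 68 = 57.12, stated as 58. The figures reproduce. Under independence the ANCOVA has power of 82% at 58, 83% at 60 and 92% at 80.

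**2. Partially nested variance.** With n per arm, group size m and residual variance 1 − 0.16 = 0.84:

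- Var(MBT-P mean) = 0.84 × [1 + (m − 1) × ICC] / n
- Var(TAU mean) = 0.84 / n
- Satterthwaite df = (sum of the two variances)² / [Var(MBT-P)²/4 + Var(TAU)²/(n − 1)], where 4 = 5 groups − 1

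Example, N = 60 and ICC = 0.10: Var(MBT-P) = 0.84 × 1.5 / 30 = 0.042; Var(TAU) = 0.84 / 30 = 0.028; SE = √0.070 = 0.265; noncentrality = 0.7 / 0.265 = 2.65. With 57 df the power is 74%. The Satterthwaite df are 0.070² / (0.042²/4 + 0.028²/29) = 10.5, and the power is then 67%.

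**3. Type I error of the planned test.** Simulated with no treatment effect, the clustered MBT-P arm and an analysis that ignores group. Separate runs differ by a few tenths of a percentage point.

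60 analysed (5 groups of 6):

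| ICC | Type I error | Power, variance inflation only (57 df) | Power, Satterthwaite df |
|---|---|---|---|
| 0 | 5.0% | 83% | 78.6% |
| 0.02 | about 5.5% | 81% | 76% |
| 0.05 | about 6.4% | 78% | 73% |
| 0.10 | about 7.9% | 74% | 67% |
| 0.15 | about 9.6% | 70% | 62% |

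80 analysed (5 groups of 8):

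| ICC | Type I error | Power, Satterthwaite df |
|---|---|---|
| 0 | 5.0% | 89% |
| 0.02 | about 5.7% | 86% |
| 0.05 | about 6.9% | 82% |
| 0.10 | about 9.2% | 75% |
| 0.15 | about 11.5% | 69% |

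**4. Two separate sources of power loss.** At N = 60 and ICC = 0, moving from 57 df to Satterthwaite df already lowers power from 82.8% to 78.6%. About 4 points are therefore the price of having only five groups; the rest comes from the correlation itself.

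**The case against.** The strongest reply is that the protocol gives no ICC, so the harm is conditional. That stands. At ICC 0.02 the type I error is about 5.5% to 5.7%, which is close to harmless. A reader might infer that the power is simply wrong and every p-value too small; the documents do not support this, because both statements need a positive ICC of some size. The remarks on belonging and group dynamics make one plausible but do not quantify it.

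Second, recruiting 80 against a need of 58 leaves slack, and the pilot's drop-out was only 10% over one year. This stands in part. If all 80 are analysed, 80% power survives to about ICC 0.05 even on Satterthwaite df. But the plan sets that slack aside for drop-out, and larger groups make the type I inflation worse.

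Third, part of the lower power comes from the df of the proposed model. This also stands, which is why the two effects are shown apart.

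The same section invites two further complaints: it states the planning effect for social cognition, not social functioning, and its social-functioning source has a confidence limit down to 0.37. Neither belongs to this point. The cited effects and ρ concern social functioning or related social outcomes, so the wording changes no number. Power at a lower confidence limit is a question about a planning assumption, unrelated to therapy groups.

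**Conclusion.** The point holds in conditional form. The sample size and the fixed single-level ANCOVA leave out the therapy groups of the MBT-P arm. With a positive ICC the primary test is anti-conservative and the stated power optimistic. At a mid-range ICC of 0.05 to 0.10, a nominal 5% test has a real error of about 6.4% to 7.9% with 60 analysed and 6.9% to 9.2% with 80. Power at 60 is then 78% to 74% from variance inflation alone, or 73% to 67% on Satterthwaite df.

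These sizes rest on the assumed ICC, even group sizes and equal total residual variance. Correlation through shared individual therapists is not included. The result does not show that the trial is too small, and it is not a case for a larger N.

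**What to change.** Replace the plain ANCOVA for the primary outcome with a partially nested mixed model: baseline SFS, treatment, a random therapy-group intercept in the MBT-P arm only, arm-specific residual variance, and Satterthwaite or Kenward-Roger df. Do likewise for the secondary outcomes now given an ANCOVA, each with its own baseline.

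Because the analysis is by intention to treat, state in advance how MBT-P patients who never join a group are handled: as singleton clusters, or in the group to which they were assigned. Let the multiple-imputation model allow for therapy group.

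Restate the power at 60 and at 80 analysed over a stated ICC range such as 0.02 to 0.15, with no change in N.

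The cost is wording, a record of group membership, a less favourable stated power and fewer df. With only five groups the group variance will be poorly estimated, and the report should say so.
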